## Abstract

**Background:**

This paper describes the rationale and design of the ENVIS-ion Study, which aims to determine whether low-dose aspirin reduces the development of white matter hyper-intense (WMH) lesions and silent brain infarction (SBI). Additional aims include determining whether a) changes in retinal vascular imaging (RVI) parameters parallel changes in brain magnetic resonance imaging (MRI); b) changes in RVI parameters are observed with aspirin therapy; c) baseline cognitive function correlates with MRI and RVI parameters; d) changes in cognitive function correlate with changes in brain MRI and RVI and e) whether factors such as age, gender or blood pressure influence the above associations.

**Methods/Design:**

Double-blind, placebo-controlled trial of three years duration set in two Australian academic medical centre outpatient clinics. This study will enrol 600 adults aged 70 years and over with normal cognitive function and without overt cardiovascular disease. Subjects will undergo cognitive testing, brain MRI and RVI at baseline and after 3 years of study treatment. All subjects will be recruited from a 19,000-patient clinical outcome trial conducted in Australia and the United States that will evaluate the effects of aspirin in maintaining disability-free longevity over 5 years. The intervention will be aspirin 100 mg daily versus matching placebo, randomized on a 1:1 basis.

**Discussion:**

This study will improve understanding of the mechanisms at the level of brain and vascular structure that underlie the effects of aspirin on cognitive function. Given the limited access and high cost of MRI, RVI may prove useful as a tool for the identification of individuals at high risk for the development of cerebrovascular disease and cognitive decline.

**Trial Registration:**

clinicaltrials.gov Identifier: NCT01038583

## Background

Cognitive decline and dementia are major causes of morbidity and mortality worldwide and are substantially burdensome to the affected persons, their caregivers, and society in general [1]. Despite extensive research over the past 20 years, there remain important and formidable challenges to conducting research, particularly into the area of prevention. A recent National Institutes of Health Consensus Development Conference concluded that large-scale population-based studies and randomised controlled trials are critically needed to investigate strategies to maintain cognitive function in individuals at risk or those experiencing cognitive decline [1]. The Aspirin in Reducing Events in the Elderly (ASPREE) Study is one such large scale trial and this manuscript describes a neurovascular imaging sub-study (ENVIS-ion) that will explore the possible mechanisms through which aspirin may act to influence cognitive function.

### Rationale for the ENVIS-ion Study

A decline in cognitive abilities is commonly held to be an inevitable consequence of aging with greater degrees of decline suggesting the superimposition of progressive neuropathology. Even in healthy older adults, a small but definite age-related decrease in performance on executive function, verbal fluency, verbal memory, and cognitive speed tasks is evident [2], but the mechanisms leading to decline are not completely understood [3]. Similarly, reports of the effects of preventive interventions on the trajectories of changes of brain structure and cognitive performance with aging and early dementia are scarce. Nonetheless, it is clear that in adults over 70 years of age with declining cognitive performance, up to 15% per year will cross the threshold for the diagnosis of clinical dementia [4,5].

Ischaemia of brain white matter may cause cognitive decline in its own right, but it is also present in the majority of those with Alzheimer's (AD). Vascular risk factors have emerged as important contributors to the development of AD and to sub-clinical brain infarcts/ischaemia. This is the most common pathology found in community-based studies of older adults with cognitive decline [6,7]. Therefore, vascular disease is an attractive target for primary preventive therapy.

The question of whether low-dose aspirin might be protective against cognitive decline, presumably via an effect on platelet aggregation, remains unanswered. Several community-based, prospective studies and a cross-sectional study have suggested an association of aspirin treatment with preservation of either episodic memory or global cognitive performance [8]. Further studies have contradicted these results and found that long-term use of aspirin does not provide benefits for cognition among generally healthy women aged 65 years or over and may even increase the risk of development of AD [9,10].

However a number of studies have demonstrated the effective use of aspirin in the prevention of other conditions such as stroke, coronary heart disease events and diabetes. Aspirin has been shown to reduce the risk of serious vascular events (non-fatal myocardial infarction, non-fatal stroke, or vascular death) by about one quarter, in high-risk patients [11].

### Magnetic Resonance Imaging (MRI)

Brain MRI changes correlate with white matter ischaemia/infarction and MRI is commonly used to investigate the underlying mechanisms and predictors of dementia and cognitive decline [7]. MRI can assess brain structure changes using volumetric tissue measurements, or intensity-based lesion identification to quantify structural changes such as hyper-intense white matter lesions (WMH) or infarcts. The association of greater WMH volume with poorer cognitive performance remains a focus of ongoing research. While some studies have found that WMH presence and volume rather than location determines the presence of executive dysfunction in those who are non-demented, others have specifically related periventricular WMH to such cognitive dysfunction [12]. Silent brain infarcts (SBI) are frequently seen on MRI in healthy older adults and are associated with dementia incidence and cognitive decline as well as subsequent clinical stroke [13,14]. The Rotterdam Stroke Study found that the presence of SBIs at baseline more than doubled the risk of dementia [14]. In addition, the presence of SBIs at baseline was associated with poorer initial cognitive performance and a steeper decline in global cognition. Also, the incidence of SBI increased markedly with age and a prevalent SBI at baseline strongly predicted a new silent infarct on the second MRI [15]. The authors concluded that the cardiovascular risk factors for SBI are similar to those for stroke.

The preventive effects of aspirin on MRI-detected SBI and WMH have previously been investigated. A study by Sato et al. found that in patients with non-valvular atrial fibrillation (NVAF), and perhaps also those in sinus rhythm, aspirin may reduce SBIs [13]. Fujita et al. also reported a significant reduction in progression of WMH over 4 years with aspirin treatment for those with corrected platelet hyper-aggregability in a study of older, treated patients compared with age- and WMH-matched controls [10]

### Retinal Vascular Imaging

While brain MRI can potentially provide an efficient surrogate for cognitive decline and dementia, it is costly and not widely accessible, making it impracticable for population screening. Retinal vessels share many features with the cerebral vasculature. Hence, should changes in the two be highly correlated, retinal digital photography through non-dilated pupils would provide the opportunity to combine a relatively inexpensive, rapid, widely available tool with automated analysis to assess cerebrovascular pathology and inform selection of those likely to benefit most from further investigation and preventive therapies.

It is well known that clinically detectable changes in retinal blood vessels (retinal arteriolar narrowing, arteriovenous nicking, microaneurysms, retinal hemorrhages and cotton wool exudates) are markers of the effects of chronic hypertension and other vascular processes [16,17]. Because the retinal circulation can be viewed non-invasively, it offers a unique insight into the cerebral microcirculation in vivo and may allow a greater understanding of cerebrovascular pathophysiology [16]. Retinal and cerebral arteriolar histopathologies are highly correlated in those who have died of stroke, while retinal microvascular flow is reduced in persons with WMH and SBI on MRI [18].

Large population-based studies have shown that retinal vascular changes are associated with subclinical and clinical cerebrovascular disease, including cognitive impairment [16,19]. Other studies have demonstrated that changes in RVI parameters have been associated with poorer cognitive performance in people with diabetes [15,20]. In the Atherosclerosis Risk in Communities (ARIC) study, RVI changes on photomicrography were associated not only with incident stroke, but also with subclinical changes in MRI-defined parameters, including cerebral infarction, WMH (both sulcal and periventricular) and atrophy [21-23]. Furthermore, the ARIC study demonstrated that in patients without a previous stroke, retinal vascular changes were associated with poorer cognitive function independent of traditional risk factors [21]. However this study was unable to correlate changes in cognition with RVI changes over time. Similar studies have also examined the relationship between RVI changes and WMH volume [24]. Retinal arterial pathology, especially retinal arterial sclerosis and narrowing, has also been shown to correlate with MRI signs of cerebral small-vessel disease in both hypertensive and normotensive subjects [25]. In summary, there are few studies that have examined the effect of aspirin on MRI-detected SBI and WMH and RVI parameters and their relationship to cognition. Importantly, RVI may be a relatively inexpensive, more widely available imaging tool that could be used to screen and predict the onset and progression of subclinical cerebrovascular disease.

### The ENVIS-ion trial

The ENVIS-ion trial is designed to determine whether;

a) low-dose aspirin reduces the development of WMH and SBI as assessed by MRI,

b) a reduction in changes in RVI parameters is observed with low-dose aspirin therapy,

c) changes in RVI parameters parallel changes in brain MRI,

d) baseline cognitive function correlates with baseline MRI and RVI parameters,

e) changes in cognitive function correlate with changes in brain MRI and RVI, and

f) factors such as age, gender, education or blood pressure influence the above associations.

## Methods/design

ENVIS-ion is a multi-center, three-year randomized, double-blind, placebo-controlled trial in 600 healthy adults without dementia recruited from general practices in Melbourne and Canberra, Australia. ENVIS-ion is a sub-study of the Aspirin in Reducing Events in the Elderly (ASPREE) clinical trial.

### The ASPREE Trial

ASPREE is a large scale, randomized double-blind placebo-controlled trial of 100 mg enteric-coated aspirin daily, which is examining the benefits and risks of such treatment in apparently healthy subjects from Australia and the United States aged 70 years or more without overt cardiovascular disease or dementia. Although low-dose aspirin has been shown to reduce the risk of vascular events in a wide range of primary and secondary care settings [6,26,27], the benefit of aspirin may be offset by a variety of adverse effects, such as gastrointestinal and intracranial hemorrhage; the balance of risks and benefits has not been established in older subjects.

### Subjects

Participants for the ASPREE trial and ENVIS-ion sub-study will be recruited from general medical practices and community advertising. General practice participants will be sent a letter inviting them to participate in the study. Following preliminary telephone screening, participants will be included in the study if they are aged 70 years of age or over, not institutionalized, provide informed consent, and are physically capable of attending their family physician and for ENVIS-ion, the MRI facility. Participants in the ASPREE parent study will be excluded if they have a history of a previous cardiovascular event, a serious inter-current illness likely to cause death within the next 5 years, a current or recurrent condition with a high risk of major bleeding, anaemia, an absolute contraindication to or allergy to aspirin, current continuous use of aspirin or other anti-platelet drug or anticoagulant, a systolic blood pressure ≥180 mmHg or diastolic blood pressure ≥105 mmHg, a history of dementia or a Modified Mini-Mental State Examination (3 MS) score ≤77, an inability to perform any one of the six Katz ADL's [28] independently or with more than 'a little difficulty', pill-taking compliance outside the range of 80-120% during placebo run-in phase, or are currently participating in another clinical trial. All ASPREE participants who have no known contraindications to MRI and can attend the MRI facility are deemed eligible for entry into the ENVIS-ion sub-study. MRI contraindications include a) cardiac pacemaker, b) non-compatible cerebral-aneurysm clip, c) cochlear implant, d) retained metal fragment in the eye and e) stapedectomy with implant. Treatment allocation will remain blinded to investigators and subjects until the conclusion of the main ASPREE Study.

### Consent and Ethics Approval

All participants will consent separately for the ENVIS-ion trial after ASPREE trial consent. Protocols (etc.) have been approved for both studies by the Monash University Health and Research Ethics Committee.

### Assessments

All participants will complete a baseline and 3-year follow-up assessment which will include ASPREE plus additional ENVIS-ion cognitive testing, MRI and RVI. Additionally, participants will complete annual ASPREE follow-up visits comprised of compliance checking by pill count, blood pressure measurement, reassessment of behavioural traits, cognitive and quality-of-life tests and biochemical markers as part of the ASPREE study (Table 1). Retention will be enhanced through telephone contact quarterly along with regular newsletter correspondence. The three year follow-up time was chosen as an optimal time-frame to allow for the potential impact of treatment and minimize loss to follow-up due to major events such as death.

**Table 1 T1:** Measurement schedule for the participants of the ENVIS-ion trial.

	Recruitment, Screening & Baseline	Annualreview (1 yr)	Annualreview (3 yr)	Annualreview (5 yr)
**ENVIS-ion study**				
Brain MRI & RVI	X		X	
Additional cognitive function tests^a^	X		X	
**ASPREE parent study**				
Inclusion/exclusion criteria; informed consent	X			
Cognitive function tests^b^	X	X	X	X
Demographics & physical measures^c^	X	X	X	X
Blood pressure & cardiovascular biomarkers^d^	X	X	X	X
Health behaviors & lifestyle measurements^e^	X	X	X	X

^a ^Stoop test (Victoria version) & Color Trails test ^b ^3 MS, Digit Symbol Modalities test, COWAT, and Hopkins Verbal hearing test ^c ^Includes first language, level of education, height, weight, abdominal circumference, family history & co-morbidity; ^d ^Includes total cholesterol, LDL-Cholesterol, HDL-Cholesterol, triglycerides, C-Reactive Protein, Hemoglobin, fasting glucose & creatinine;^e ^Includes physical activity, smoking history & alcohol use, SF-36 & IADL

### Data acquisition and storage

Data will be stored securely, anonymized by trial number, with the trial number - identity key stored separately.

### Study Medications and supplies

An initial box with placebo medication for 4 weeks will be given to participants at the screening visit to check medication compliance. If for whatever reason a participant cannot attend their randomization visit at 4 weeks, they will receive another screening visit and supply of placebo. Participants in the study will be allocated to one of two treatments: a) acetylsalicylic acid (ASA) 100 mg, administered as an enteric-coated white tablet or b) placebo, an enteric-coated white tablet with identical appearance. A 100 mg dosage was selected as this is the common international dose. Enteric coating will ensure that both the active and placebo medication have an identical taste. Randomization of drug and placebo will be achieved via interactive voice recognition software (IVRS) and will be stratified by primary care practice and age. Subsequent to the randomization visit each participant will be provided with 12 months' supply of study drug; either aspirin or placebo. At each annual visit each participant will be provided with the next 12 months supply of their allocated drug. ENVIS-ion participants will continue receiving randomized therapy for the remaining two years of the ASPREE main trial after completing their involvement in the ENVIS-ion study.

### Cognitive testing

Cognitive testing for the parent ASPREE trial consists of i) the Modified Mini-mental State examination as a test of general intellectual function, on which participants must score > 77/100 at entry [29]; ii) a single-letter ("F") Controlled Oral Word Association test (COWAT), which gives equivalent information to the longer 3-letter tests, as a measure of fluency [30]; iii) the Hopkins Verbal Learning Test-Revised as a measure of verbal anterograde episodic memory [31]; and iv) an alternative version of the Digit-Symbol Modalities test as a measure of psychomotor speed [32]. The Center for Epidemiological Studies - Depression Scale (CES-D) is also included in the ASPREE battery for later analysis as a covariate [33]. In addition to the cognitive function testing in ASPREE, ENVIS-ion participants will complete the Stroop test (Victoria version) as a measure of cognitive inhibition, and the Color Trails test, which is a non-language based test of sequencing, alternation and processing speed [32,34-36].

The emphasis on aspects of executive functioning (COWAT, Stroop, Color Trails) and processing speed (SDMT, Color Trails) reflects the typical neuropsychological pattern seen with cognitive impairment due to subcortical ischaemic damage [37], the focus of this study. The choice of test battery is based on the neuropsychological batteries suggested for assessment of vascular cognitive impairment [38]. Assessors will undergo standard training and assessment of the administration of tasks and this will be recertified on an annual basis and if the number of assessments falls below three in a three month period.

### Magnetic Resonance Imaging

A non-contrast MRI examination will be performed on all participants at either the Canberra or Alfred Hospitals at baseline and 3 years later using 1.5 Tesla Siemens and GE machines respectively. A number of standardized MRI Brain sequences will be acquired to allow morphologic, microstructure and functional assessment. First, a volumetric 3D T1-weighted sequence is used to obtain high resolution anatomical information. This is followed by the FLAIR and T2 sequences used to assess inflammation and signal alteration in brain tissues. A Gradient Echo T2-weighted (GE T2) or Susceptibility Weighted Imaging (SWI) sequence will be used to detect micro-hemorrhages. Where technically possible, Arterial Spin Labeling (ASL) will be used to quantify brain perfusion without the need to use exogenous contrast agents. Finally, Diffusion Tensor Imaging (DTI) data will be acquired to evaluate underlying neural tissue diffusion properties, permitting assessment of complex brain microstructure (e.g. axonal loss in white matter tracts).

MRI analyses will be performed at the Dementia Collaborative Research Centre Imaging Laboratory in Canberra. All assessment will be conducted blinded to treatment allocation and participant data. Standard pre-processing for all volumetric images will follow best practice that has been developed for such studies with large numbers of participants [39]. This includes; 1) N3 B0 MRI nonlinear intensity distortion correction, between-scan intensity normalization and registration to a population-specific model that is then later matched to the ICBM model of cortical anatomy; 2) model-based segmentations of whole brain, ventricular, lobar and hippocampal volumes; 3) white matter/grey matter (WM/GM) segmentation: a multi-spectral segmentation utilizing all acquired data types will provide a good measure of the CSF and WM/GM volumes, and consequently, accurate atrophy measures as well as lobar WM/GM differences; 4) nonlinear registration of the EPI T2 from the functional scans to the gradient echo volumetric T2. The GE T2 will then be matched to the volumetric T1 and then to the ICBM model using an iterative nonlinear registration to reduce within-group subject differences at time steps.

Calculations will be made from the scans regarding WMH with respect to their total volume and rate of change in volume. The presence or absence of sub-cortical infarction will be determined and the total brain volume calculated. The presence and count of cerebral micro-bleeds will be determined from the GE T2 and SWI data and brain tissue perfusion will be assessed from the ASL scans. Volumetric change of structures including the hippocampus and ventricles will be assessed via the automated comparison of each of the individuals to average models of anatomy.

### Retinal Vascular Imaging

Two color retinal photographs, centered on the optic disc (ETDRS standard fields 1 (Figure 1)) and macula (standard field 2), respectively, will be taken from each eye of the participant. The photographs will be taken after 5 minutes of dark adaption, without pharmacological pupil dilation, using a Canon NMR 45 digital fundus camera. Photographers are certified for quality of measurement by the central reporting group prior to the commencement of the study.

**Figure 1 F1:**
[figure not shown]
**Retinal Vascular Imaging measurement of Retinal Calibre**.

RVI images will be sent to the core analysis laboratory at the Retinal Vascular Imaging Centre in Melbourne for analysis by trained graders. Photographs centered on the optic disc of each eye will be examined using standard computer-assisted retinal analysis software that was initially developed for the ARIC study [40]. The grading approach measures retinal vessel diameters and combines the measurements into central retinal arteriolar and venular equivalents (CRAE and CRVE) with formula adjusting for branching, following the Parr and Hubbard formula [40]. The analysis software has been modified and improved, and used in a number of studies including the Australian Diabetes, Obesity and Lifestyle Study (AusDiab) and the Blue Mountains Eye Study (BMES) in Australia [41]. The graders will use an automated system to measure the calibers of all arteriolar and venular branches crossing a zone defined as the region between 1/2 and 1 disc diameter from the optic disc. The grader will monitor the whole process, carefully select appropriate vessel regions for caliber measurement and correctly identify small arteriolar and venular branches. Correction factors are used in analysis of the measured values of absolute vessel caliber. All grading will be conducted blinded to treatment allocation. Technically unsatisfactory scans are typically not improved by re-photography, and will not be included in the analysis.

The qualitative presence of focal retinal arteriolar narrowing, arteriovenous nicking, arteriolar wall opacity ("silver wiring") and the presence of retinopathy lesions will also be assessed. Each lesion is classified as definite, questionable/probable, or none in each of the retinal photographic fields.

### Sample size

Approximately 300 participants each from Melbourne and from Canberra, Australia will be enrolled in ENVIS-ion. The sample size calculations were based on a) a pilot study of 144 older adults, in which acceptance of MR imaging was 88%, and which produced MR imaging estimates of change in relevant structural brain parameters over a two-year period; b) rate of change of WMH over 3 years from the PROSPER trial of adults aged 70 years or over [42]; and c) cautious interpretation of the report by Sato et al., in which treatment with around 300 mg/day of aspirin over one year reduced incident SBIs on MRI from 20.6% to 9.6% in 150 participants with non-valvular atrial fibrillation (i.e. a relatively higher risk group than in ENVIS-ion) [13,43]. Based on power calculations related to the primary hypothesis, we conservatively estimate the need for at least 230 per treatment arm to achieve a statistical power of 0.9 to show a relative risk reduction of 15% with a 2-sided α of 0.05.

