### Statistical analysis

Group descriptive statistics will be used to define the baseline characteristics of subjects randomized to aspirin and placebo groups. Continuous variable changes will be normalized prior to analysis and non-parametric methods will be used where required. Changes in continuous variables for both MRI and RVI over three years will be analyzed using analysis of covariance (ANCOVA) adjusting for baseline values (Aims 1,2 & 5). Chi-square and logistic regression analysis will be used to assess changes in categorical variables. Correlation and regression analysis will be used to determine the association between changes in MRI and RVI measures and the association of baseline cognitive measures with MRI and RVI parameters (Aims 3 & 4). Generalized linear models will be developed to determine whether age, gender, education, previous aspirin use and hypertensive status modify the treatment effects on MRI and RVI outcome measures (Aim 6).

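### One power of 0.9 and one alpha of 0.05 are quoted for an undefined primary hypothesis, while the main aim names both WMH and SBI; at the stated 15% reduction that power cannot hold for SBI

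*Protocol article*

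**What the plan says.** The list of aims under The ENVIS-ion trial opens with whether "low-dose aspirin reduces the development of WMH and SBI as assessed by MRI". The Abstract states the same pair as the study's aim and describes the remaining aims as additional. Neither place ranks the two outcomes.

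The Sample size section draws on inputs for both: a three-year rate of change in WMH from a cited trial, and a cited one-year fall in new SBI from 20.6% to 9.6% in a group it describes as higher risk than this trial's. The resulting figure, "Based on power calculations related to the primary hypothesis", is 230 in each arm. The target power is 0.9, and the trial is sized "to show a relative risk reduction of 15% with a 2-sided α of 0.05". The hypothesis is not spelled out, and no endpoint, control risk, mean or SD is attached to the 15%.

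The section Magnetic Resonance Imaging treats WMH as a volume with a rate of change, and sub-cortical infarction as present or absent. Under Statistical analysis, changes in continuous MRI and RVI variables go to ANCOVA adjusted for baseline, with Aim 1 among the aims listed. For the rest, "Chi-square and logistic regression analysis will be used to assess changes in categorical variables", with no aim number attached.

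**The concern.** The main aim needs at least two tests if WMH is a volume and infarction is present or absent, yet only one power and one alpha are given. A reader cannot tell which outcome they describe. The term relative risk reduction suggests a binary endpoint, which points to SBI, but 230 per arm is far too few for SBI at 15%.

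Two things are at stake. First, a null SBI result could be read as coming from a trial with 90% power, when power was much lower. Second, with no named primary endpoint, a claim of benefit could after unblinding rest on whichever outcome reached p < 0.05, and the quoted alpha and power would not describe that claim.

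**Working it through.** **Inputs from the article.** n = 230 per arm, power 0.9, two-sided alpha 0.05, relative reduction 15%, cited SBI risks 20.6% and 9.6% over one year (all Sample size); 1:1 allocation (Abstract). Not given: three-year SBI control risk, WMH mean change, WMH SD, and the correlation between the two tests. These are varied below as assumptions.

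**1. Can 230 per arm be reproduced?** Not from what is stated.
- As SBI with a 15% reduction from 20.6% (to 17.5%), 0.9 power needs 3,393 per arm (3,458 with continuity correction).
- The full cited SBI effect, 20.6% to 9.6%, needs 221 per arm (239 with continuity correction). That is close to 230, but it is a reduction of (20.6 − 9.6)/20.6 = 53%, not 15%.
- As WMH, it depends on an SD that is not given (step 3).

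**2. Power for SBI at 230 per arm.** With p2 = 0.85·p1 and pbar = (p1 + p2)/2,

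power = Φ[(p1 − p2 − 1.960·SE0)/SE1], where SE0 = √(2·pbar(1 − pbar)/n) and SE1 = √((p1(1 − p1) + p2(1 − p2))/n).

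- p1 = 0.206: difference 0.0309, SE0 = 0.03662, SE1 = 0.03659, so Φ(−1.117) = 0.13. With all 300 per arm evaluable it is 0.16.
- One-year risk assumed to compound over three years: p1 = 1 − 0.794³ = 0.499, difference 0.0749, SE0 = 0.04649, SE1 = 0.04636, so Φ(−0.350) = 0.36 (0.37 if the unpooled SE is used throughout). With 300 per arm, 0.45.
- Lower assumed risks of 15% and 9.6% give 0.10 and 0.08.
- Solving for 0.90 gives p1 = 0.838, a control risk of about 84%.

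**3. Power for WMH at 230 per arm.** For a 15% smaller mean change, power = Φ[0.15/((SD/mean)·√(2/230)) − 1.960]. Power of 0.90 requires a standardised difference of (1.960 + 1.282)·√(2/230) = 0.302, so SD/mean = 0.15/0.302 = 0.496.

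| Assumed SD/mean | Power at 230 per arm | n per arm for 0.90 |
|---|---|---|
| 0.496 | 0.90 | 230 |
| 0.6 | 0.76 | 337 |
| 0.8 | 0.52 | 598 |
| 1.0 | 0.36 | 934 |

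**4. What the single alpha and power would mean under each success rule.**
- Either outcome suffices, each at 0.05, no adjustment: 1 − (1 − 0.05)² = 0.0975 if the tests are independent. From the bivariate normal, 0.091 at an assumed correlation of 0.5 and 0.070 at 0.9.
- Both must succeed: alpha is not inflated. If each test had power 0.9, joint power would be 0.9² = 0.81 at correlation 0, 0.83 at 0.5 and 0.87 at 0.9. With SBI power at 0.13, joint power cannot exceed 0.13.
- WMH alone is primary: alpha is 0.05, and the power is whatever the WMH inputs support.

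**The case against.** The strongest answer is that the article never says both outcomes are primary. An aim naming two markers does not declare two tests at 0.05. The Statistical analysis section ties Aim 1 only to ANCOVA of continuous changes. The chi-square and logistic sentence names neither SBI nor an aim and could serve the categorical retinal signs, and the Discussion even speaks of SBI volumes. If WMH was powered and SBI is supportive, no error rate is inflated. Endpoint hierarchy and alpha allocation also commonly sit in the full protocol or SAP, which are not shown. In addition, 20.6% is a one-year risk in atrial fibrillation patients, and this is a mechanistic sub-study.

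Most of this stands. A reader might infer that the plan nearly doubles its false-positive rate. The article does not support that: it states no either-endpoint rule, and 9.75% also requires independence and no adjustment. Nor is it a finding that the article lacks a multiplicity rule.

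What the objection does not remove is the power statement. The article names SBI in its main aim, uses SBI incidence as a sample-size input, and quotes a 15% relative risk reduction with 0.9 power. Longer follow-up does not rescue that: compounding to about 50% gives about 0.36, and 84% would be needed in a group the article itself calls lower risk than the cited one.

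**Conclusion.** The point holds in a limited form. The article attaches one n, one power and one alpha to an undefined primary hypothesis, and the power is not true of one of the two outcomes in its main aim. For SBI at a 15% relative reduction, power at 230 per arm is about 0.13 at the cited risk and about 0.36 under assumed three-year compounding. This rests on SBI being analysed as present or absent, as the MRI section indicates, and on a control risk well below 84%.

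The error-rate consequences are conditional. They are about 7% to 9.75% under an unadjusted either-endpoint rule and nil if WMH alone is primary or both must succeed. Power below 0.9 follows if both must succeed. The article does not say which rule applies.

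The 0.9 is not thereby confirmed for WMH. It holds there only if SD/mean is about 0.50, which cannot be checked without the mean and SD.

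**What to change.** - Name 3-year change in WMH volume as the single primary endpoint, tested at two-sided 0.05.
- Make new SBI a secondary endpoint, tested confirmatorily at 0.05 only if WMH is significant; otherwise report it as an estimate with its confidence interval.
- Restate the sample-size sentence as a 15% smaller change in WMH volume, giving the mean and SD used. If SD/mean is not about 0.50, restate the power for 230 per arm.
- Say explicitly that the 0.9 does not apply to SBI.

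If the full protocol or SAP already names the primary endpoint, the sample-size sentence need only be aligned with it.

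The change is to wording, with no added participants or scans. Its cost is that SBI alone could not support a confirmatory claim, which is a small loss given the power shown. Splitting alpha at 0.025 each would keep both outcomes in play, but a test with 0.90 power at 230 per arm would fall to 0.84 and need about 272 per arm to recover 0.90. It would not repair the power for SBI.
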